### Eir for systematic electronic symptom assessment

Eir is an Internet-based communication platform introducing a standardized way of assessing and immediately using the patients’ self-report of symptoms in clinical consultations. The intention behind the development of Eir was to improve symptom management by:
Systematic symptom assessment and management;Timely presentation of symptoms to HCPs, regardless of location of patients and HCPs (oncology unit, outpatient unit, home, hospice, etc.);Facilitating patient-centered communication by immediate presentation of the most bothersome symptoms and problems;Options for providing evidence-based decision support based on patients’ symptom scores and the doctor’s clinical evaluation.

Eir is a HTML-based symptom assessment tool incorporating a limited amount of decision support based on evidence-based treatment guidelines. It is primarily based on PROs assessing subjective symptoms, functioning, and QoL. The system consists of multiple modules with the patient and doctor modules being used in the PALLiON study.

The patient module consists of multiple levels, starting with a general question about wellbeing, thereby mimicking a common introduction to a consultation. This question is followed by 19 common cancer symptoms to be ticked by the patient if present. These are identical to the ones in the European Association for Palliative Care (EAPC) basic dataset [68] supplemented by a few items of particular relevance for chemotherapy side effects, e.g. numbness in in fingers/toes. Subsequent questions are then presented to further evaluate and characterize the ticked symptoms for each patient. Most of the ticked symptoms are first scored on a numerical rating scale (NRS) of 0–10 and followed by in-depth questions depending on the NRS scores. The follow-up questions are taken from well-validated and frequently used questionnaires, such as the Edmonton Symptom Assessment System (ESAS) [69], Brief Pain Inventory (BPI) [70], Subjective Global Assessment for nutritional status (SGA) [71], Patient Health Questionnaire-9 (PHQ-9) [72], and European Organisation of Research and Treatment of Cancer Quality Of Life Questionnaire Core 15 Palliative (QLQ-C15-PAL) [73].

Patients respond to the questions on a tablet that is connected to WiFi. The responses are immediately transferred and stored at a secure server that can be accessed by the HCP who logs on to the doctor module on a free-standing computer (not connected to the hospital’s intranet). The most recent PROs are presented, supplemented by a graphical display showing the development of symptoms over time if the patient has been seen before. Furthermore, treatment advice can be viewed on the physician’s computer screen. For example, suggestions to start pain medication, change the dose, switch to another drug, adding laxatives, etc. may pop up, based on the patient’s present and previous pain scores. Current performance status and weight changes are displayed on top of the screen.

The Eir system was evaluated and approved by HEMIT [74] in 2015. The thorough evaluation focused on security and risks, in the form of a risk and vulnerability analysis. No security violations or serious risks were detected. The use of Eir will be performed in accordance with regulations and standards at each of the six intervention hospitals that will use Eir as part of the care pathways.

### The patient-centered care pathways

A PCCP in PALLiON means that the planned treatment trajectory for *the individual* patient is outlined and presented to the patient and caregivers shortly after inclusion in the study. The PALLiON pathways are easily accessible on all hospital and free-standing computers by a shortcut key, to the front page (Fig. 1). The pathways are developed for everyday clinical use in that they guide the physicians’ and other healthcare providers’ actions and responsibilities in the four sub-pathways depicted by the white arrows in Fig. 1. The content corresponds with national recommendations for treatment and follow-up for the respective diagnostic groups [75], and the former and updated national strategies for cancer in Norway [76, 77].

**Fig. 1 Fig1:**
[figure not shown]
The patient-centered care pathways and supplemental information *. * arrows and boxes are interactive and contain essential aspects and additional information for each step of the pathway

For each of the four sub-pathways or phases in Fig. 1, i.e. chemotherapy, transition to post-chemo, post-chemo, and EoL care, the tasks of the involved physicians are clearly defined, as illustrated in the chemotherapy pathway in Fig. 2. The pathways will ensure more standardized treatment decisions, systematic evaluation of treatment effects and side effects according to established criteria, i.e. CTCAE Common Terminology Criteria for Adverse Events [78] and RECIST Response Evaluation Criteria In Solid Tumors [79], regular symptom monitoring using Eir, and a structured integration between the oncologist and the PC team at defined timepoints. They include different clinical scenarios that may become relevant during the last year of life, e.g. rapid disease progression, frailty, treatment toxicity, etc. Involvement of patient and caregiver is specifically focused in all consultations. The high level of details aims to improve the predictability of the disease trajectory during the last year of life and allows for adaptations based on continuous clinical considerations and patients’ and caregivers’ preferences as death comes closer.

**Fig. 2 Fig2:**
[figure not shown]
The chemotherapy pathway

The chemotherapy pathway as shown in Fig. 2 consists of carefully selected factors that together constitute a predictable trajectory that integrate oncological and PC for patients and caregivers.

These key factors encompass:
Clinical outcomes and PROs as these variables constitute an important premise for the decision-making regarding start, pause, or discontinuation of chemotherapy and/or other treatment strategies;Formalized, continuous collaboration between oncology and PC starting at study inclusion, with a compulsory PC consultation for all patients and caregivers;Defined responsibilities, by explicitly stating who is the primary responsible physician, the oncologist or the PC physician, depending on where the patient is in the trajectory;Systematic inclusion of patient preferences and active participation in decision-making;Involvement of family members upon start of last line of chemotherapy, and onwards;Explicit, shared, and delegated patient and caregiver responsibilities and information;Systematic symptom assessment with Eir as part of the standardized care pathway;Systematic transfer of information between the hospital, general practitioners, and the community health services;Multi-professional collaboration with referrals as needed.

All patients in the intervention arm will have regular follow-up during the disease trajectory by the PC team both within and outside of hospital, with regular assessments of PROs (symptoms, psychological distress, social support) with phone calls approximately every other week, PC consultations as needed, and assessment of need for home care or nursing home admissions.

### The control arm

Patients in the control arm will be included when coming for start of what is the anticipated last line of chemotherapy as the same inclusion criteria apply as for patients in the intervention arm. Anticancer and other medical treatment, PC, and patient follow-up will be conducted according to established guidelines. Symptom management, contact with the hospitals’ PC teams, referral to other HCPs, care and contact with caregivers, and use of healthcare services will follow common practice. HCPs will register these activities in the e-CRFs (Table 4).

**Table 4 Tab4:**
[figure not shown]
Study schedule, according to the Standard Protocol Items: Recommendations for Interventional Trials (SPIRIT) guidelines

^1^Self-reported data are collected up to seven times during the first year, or until the patient’s death or study withdrawal, whichever comes first. As final date for inclusion is 31 December 2020, patient follow-up will continue in 2021

^2^Caregivers receive two forms at 6 and 12 months after the patient is dead, provided that they consent to continue in the study. Thus, caregiver follow-up may continue in 2022

^3^Educational program for physicians to be completed before patient enrolment

^4^All study forms are similar in both arms

^5^Sociodemographic data that are unlikely to change over time are only registered at baseline

### Withdrawal criteria

Patients may withdraw from the study at any time at their own request. They receive information that they do not need to explain the reason for withdrawal. If a patient decides to discontinue the study, we confirm that the request is received. We will also ask if the patient consents to the use of data that have already been collected. If not, the previously collected data are deleted.

### Trial procedures

Table 4 shows the study timeline and all data registrations from enrolment to end of study, according to SPIRIT guidelines.

### Data collection and statistics

#### Data registration by study personnel

##### Patients

An e-CRF, developed by the Unit for Applied Clinical Research at NTNU, is used for registration of clinical data, every other month until death or for 1 year. This is the responsibility of the study nurses and Principal Investigators at the participating sites. The first questions of the initial CRF contain confirmation of written informed consent and whether the caregiver can be asked to participate. These items are not replicated in subsequent registrations. The clinical variables are: height; weight; cognition (date, time, day, backwards spelling); co-morbidities; principal cancer diagnosis and date of diagnosis; stage; presence; site and number of metastases; previous and present anticancer treatment (within the past 2 weeks); Karnofsky Performance Status (KPS) score [80]; regular use of medication; current use and dosage of opioids; and the following biomarkers if within the past 7 days: C-reactive protein; hemoglobin; leukocytes; thrombocytes; albumin; GT (Gamma-glutamyltransferase); LD (Lactate-dehydrogenase); creatinine; and contact with the community healthcare services and general practitioner. The same set of variables are registered during follow-up, supplemented with detailed registrations of all anticancer treatment, other medical interventions, change of medication, imaging (X-ray, MRI, CT and PET scans), transfusions, and more administrative data, such as department category for treatment, i.e. palliative or general oncology unit, in- or outpatient status, and emergency or other hospital admissions.

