Explorative	To examine length of survival	Length of survival from start of last line of chemotherapy	HCP registrations, Cause of Death Registry
	To examine direct costs	Costs of healthcare, oncology/palliative units	Length of stay, number of hospitalizations, anticancer and other medical interventions

*e-CRF* electronic case report form, *EoL* end-of-life, *HCP* healthcare provider, *PRO* patient-reported outcome, *QoL* quality of life

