### Sample size

Sample size calculation was based on the primary endpoint: the proportion of patients who receive chemotherapy during their last 3 months of life (Table 1). This took into consideration the predetermined number of 12 as the total number of clusters, i.e. hospitals, that was chosen for contingency/feasibility reasons and allowing for intra-cluster correlation coefficient (ICC) in the range of 0.06–0.09, which is usually considered appropriate for process outcomes. In addition, calculations were performed to provide 80% power at the two-sided 5% level to detect a 25% difference in chemotherapy use between the two arms, i.e. 20% versus 45% in the treatment and control groups, respectively [61]. The choice of the clinically relevant treatment effect used for sample size calculation (25% difference for chemotherapy administration) was based on both clinical judgment and previous data [62, 63]. Effects on power increase due to adjustment by baseline measurements and other covariates (see statistical analysis section for the full list of covariates proposed) were also considered, allowing for correlation coefficient between outcome and adjustment covariates (r_adj_) up to 0.4. Table 2 reports sample size per treatment arm for various values of ICC and (r_adj_).

**Table 2 Tab2:** Sample size per treatment arm for various values of ICC and (r_adj_)

			**r**_**adj**_		
	*0.4*	*0.3*	*0.2*	*0.1*	*NO*^a^

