**ICC**					
*0.06*	102	120	138	150	150
*0.07*	126	150	180	198	204
*0.08*	156	204	258	**300**^b^	312
*0.09*	210	318	468	630	714

*ICC* intra-cluster correlation coefficient, *r*_*adj*_ correlation coefficient between outcome and adjustment covariates

^a^No adjustment for baseline covariates

^b^Required no. of patients per arm

A sample size of 300 patients in each arm, with a total of 600 patients, was chosen as it accounts for an ICC up to 0.08 even with a low r_adj_ (no less than 0.1) and for an ICC up to almost 0.09 in case of r_adj_ no less than 0.3. Due to an expected attrition rate up to 12%, 340 patients per arm (680 in total) will be enrolled.

The 12 hospitals were grouped into three strata according to size of catchment area, to decrease the chance of imbalance in cluster characteristics between trial arms. Each cluster consisted of four hospitals: small (69,000–136,000 inhabitants); medium (169,000–282,000 inhabitants); and large (300,000–492,000 inhabitants) (Table 3). This procedure is considered a reliable and easy to measure proxy for other cluster characteristics, potentially impacting on the study outcome. Effect of the variability in cluster size (mean 50, SD 19.5, CV [Coefficient of variation] = 0.39) was calculated through the approach proposed by Van Breuckelen [64]. For CV = 0.39, this method indicates low inflation factors which are in the range of 2.8%–2.2%, for ICC in the range of 0.06–0.09, respectively [64]. The role of the correlation coefficient in sample size formula for binary outcomes and when adjusting for baseline factors is explained by Hemming et al [65]. Sample size calculations in Table 2 were undertaken using the module clustersampsi [65] implemented in the statistical package Stata (Stata Statistical Software, Release 14, Stata Corp., College Station, TX, USA).

**Table 3 Tab3:** Presentation of stratification, randomization results, and sample size at cluster level

Intervention arm				Control arm			
Hospital	Stratification	Inhabitants	Patients	Name	Stratification	Inhabitants	Patients
Stavanger University Hospital, Stavanger	1	352,650	85	Akershus University Hospital, Nordbyhagen	1	490,000	85
Oslo University Hospital	1	340,000	85	St. Olavs Hospital/Trondheim University Hospital, Trondheim	1	300,000	85
Østfold Hospital Trust, Grålum	2	282,600	50	Sørlandet Hospital, Kristiansand	2	170,000	50
Vestfold Hospital Trust, Tønsberg	2	233,000	50	Telemark Hospital Trust, Skien	2	169,000	50

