### Study population

#### Inclusion criteria: participant level

##### Patients

At the second level of the C-RCT, the following eligibility criteria apply to patient inclusion:
A verified metastatic or locally advanced cancer of the upper gastrointestinal (GI) tract, lower GI tract, pancreas, liver, breast, bladder, prostate, kidney, cholangiocarcinoma, or malignant melanoma;Defined as a patient in need of PC with an anticipated life expectancy of < 12 months;Scheduled to start the anticipated last line of chemotherapy (definition: tumor directed systemic therapy). Time of inclusion that is based on the decisions about last line of chemotherapy, varies by diagnosis, and is equivalent to first line in some diagnoses;Age > 18 years;Fluency in written and oral Norwegian;Physically and cognitively able to provide written consent, based on clinical criteria, e.g. not too frail or having signs of disorientation, confusion, attention deficit, poor coordination;Scheduled to receive all oncological and specialized palliative treatment at the participating hospital, i.e. residing in the local area of the including hospital;WHO performance status 0–2.

Because gynecological and lung cancer patients receive anticancer treatment at the departments of lung and gynecology in most hospitals, these diagnoses were not included.

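### Clinical registration is written to stop at 1 year, so a patient alive at 12 months would have no primary outcome, and the sample size has no separate term for such patients

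*Protocol article*

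**What the plan says.** Study objectives and endpoints, with Table 1, defines the primary endpoint as the proportion receiving chemotherapy in the 3 months before death, taken from health-care-provider registrations and the e-CRF. Under Data registration by study personnel (Patients), the e-CRF "is used for registration of clinical data, every other month until death or for 1 year"; the Abstract applies the same limit to clinical variables.

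Sample size sets 300 evaluable patients per arm and then states: "Due to an expected attrition rate up to 12%, 340 patients per arm (680 in total) will be enrolled". The eligibility criterion on prognosis reads "Defined as a patient in need of PC with an anticipated life expectancy of < 12 months". No expected 12-month survival is given.

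Statistics says that the primary analysis is run once 300 patients per arm have endpoint data, by intention to treat. Trial status stops recruitment at 680 patients or on 31 December 2020. It ends patient follow-up on 31 December 2021, or earlier once the last included patient has had 1 year or died. Table 1 gives "HCP registrations, Cause of Death Registry" as the source for exploratory survival, but does not list the registry for the primary endpoint.

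**The concern.** A look-back endpoint anchored at death needs follow-up long enough to observe the death. If clinical registration closes at 1 year, everyone who outlives that year drops out of the primary comparison.

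Two things follow. First, the analysed patients are selected by an event after randomisation. The Background says early palliative care may prolong survival, so the intervention could change who is analysed. That sits badly with the intention-to-treat statement. The missing-data sensitivity analyses under Statistics are for patient- and caregiver-reported outcomes and do not cover this.

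Second, the 40 spare patients per arm must absorb survivors as well as withdrawals (whose data may be deleted, per Withdrawal criteria) and any other loss. If they cannot, the 300-per-arm trigger is not met, and the article states no fallback.

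**Working it through.** **1. The plan's own figure.** Inputs from Sample size: "80% power at the two-sided 5% level"; "20% versus 45% in the treatment and control groups, respectively"; "the predetermined number of 12 as the total number of clusters", so 6 per arm; ICC 0.08 and r_adj 0.1 for the chosen cell of Table 2.

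- Variance term: 0.45×0.55 + 0.20×0.80 = 0.4075.
- Individually randomised n per arm, with t(0.975, 10 df) = 2.228 and z(0.80) = 0.842: 0.4075 × (2.228 + 0.842)² / 0.25² = 61.44.
- Covariate adjustment: 61.44 × (1 − 0.1²) = 60.83.
- Cluster size: 60.83 × (1 − 0.08) / (6 − 60.83 × 0.08) = 49.4, rounded up to 50; 6 × 50 = **300 per arm**.

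The stated 300 is reproduced, as are 18 of the 20 cells of Table 2 exactly; the other two differ by one patient per cluster. For attrition, 340 × 0.88 = 299.2. The sample-size arithmetic is sound.

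**2. Room for patients without an outcome.** 340 − 300 = 40, and 40/340 = 11.8%. If endpoint data stop at 1 year, at least 88.2% must die within 12 months even with no withdrawals.

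**3. Share alive at 12 months (assumption; no value in the protocol).** For a Weibull with median m months and shape k, S(12) = 0.5^((12/m)^k). Evaluable per arm = 340 × (1 − S(12)), before withdrawals.

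| Shape k | Median 6: alive / evaluable | Median 9: alive / evaluable | Longest median keeping S(12) ≤ 11.8% |
|---|---|---|---|
| 1 (constant hazard) | 25% / 255 | 40% / 205 | 3.9 months |
| 1.5 | 14% / 292 | 34% / 223 | 5.7 months |
| 2 | 6% / 319 | 29% / 241 | 6.8 months |

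Five of the six scenarios fall below 300. One (shape 2, median 6) does not.

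**4. Power.** With N evaluable per arm, DE = 1 + (N/6 − 1) × 0.08, SE = √(0.4075 × DE × 0.99 / N) and power = Φ(0.25/SE − 2.228).

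- N = 300: DE = 4.92, SE = 0.0813, power 80.1%.
- 20% alive, N = 272: 79.3%.
- 30% alive, N = 238: 78.0%.
- 40% alive, N = 204: 76.4%.

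Losing patients also lowers the design effect, so the 12 clusters limit power more than the patient count does.

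**5. Following everyone to 31 December 2021.** Assume uniform accrual from March 2017 to December 2020, so about 12 to 57 months of potential follow-up, and constant hazard λ = ln 2 / m. The share alive at cut-off is (e^(−12λ) − e^(−57λ)) / (45λ): 4.8% for median 6 and 11.1% for median 9, leaving 324 and 302 of 340 per arm with a death before withdrawals.

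**The case against.** The strongest reply is that the 1-year limit may not bind the primary endpoint. Table 1 describes a look-back from death with no 1-year limit, and its source is provider registrations as well as the e-CRF. Statistics mentions paper forms for medical data. Footnote 1 of Table 4 ties the first-year limit to self-reported data. The body of Table 4, which sets out the registrations, is not visible in the text at hand. The 300-per-arm trigger also shows that the authors knew the endpoint needs a death. This leaves room for later capture. It does not settle the matter, because the e-CRF section and the Abstract both apply the limit to clinical data, and Trial status gives a trial-level end date, not a longer window per patient.

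A reader might infer that the 12% allowance is not credible, or that 300 per arm will certainly be missed. The document does not support that: it gives no 12-month survival, and shape 2 with a median of 6 months leaves 319 evaluable. The constant-hazard rows also strain against the planned 20%. Patients enter at the start of chemotherapy, so those who start it and die within 3 months count as users, and constant hazard puts 29% (median 6) or 21% (median 9) of patients in that group.

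Nor does the 80% power collapse, as step 4 shows. One might also argue that restricting to 12-month deaths greatly raises the endpoint rate. Any figure for this depends on an assumed model for time to last dose, and a shift in level is not a demonstrated bias in the difference between arms.

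Finally, any end-of-life endpoint conditions on death, and a calendar cut-off gives unequal follow-up by entry date. Trial status says that the educational programme at the intervention sites delayed the study, so entry dates may differ by arm. Both points stand and shape the fix.

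**Conclusion.** The concern holds in a limited form. Read as written, the protocol gives no primary outcome to a patient alive at 12 months, selects the analysed set after randomisation by an event that the intervention may affect, and has no separate sample-size term for such patients. Under the assumed medians of 6–9 months and shapes 1–2, whether the trigger of 300 per arm is reached within 680 enrolled is uncertain, with most scenarios falling short before any withdrawal. The power cost is small, a few percentage points at ICC 0.08 and r_adj 0.1. The more serious issue is selection on death within a year, whose size and direction cannot be derived from the document. The survival figures are assumptions throughout, and the conclusion would lapse if the full protocol already provides for endpoint capture beyond 1 year.

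**What to change.** Separate capture of the primary endpoint from the 1-year e-CRF and questionnaire schedule:

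- For every enrolled patient, collect date of death (Cause of Death Registry, already a named source) and chemotherapy dates from the participating hospital's records, until death or a common cut-off no earlier than 31 December 2021.
- Analyse all deaths to that cut-off. State the expected share still alive separately from withdrawal, and say how patients still alive are handled under the intention-to-treat statement.
- Report the number alive and the length of follow-up by arm.
- Add a sensitivity analysis with an equal follow-up window for each patient, because entry dates may differ by arm.

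This reduces selection on death but does not remove it. At a median of 9 months under constant hazard, the 302 per arm in step 5 leaves almost no room for withdrawals, so the protocol should also say what happens if 300 is not reached. The cost is a small amount of extra record extraction at the same 12 hospitals and possibly an ethics notification; no new patients or visits are needed. If later capture is already intended, a clarifying sentence on the data cut-off, with the points on analysis and reporting above, is enough.
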